## Recruitment and output test

**Recruitment of participants:**

The subjects will be recruited by public advertisement.

**Exit (drop-out) protocol:**Deliberate decision of a person:
The exit from the study protocol is possible at any time if requested by the participant. More specifically, if participants do not wish to continue the tests, they need only to report to the examiner.

**Decision imposed:**Participants who cannot perform the tasks related to research will be excluded from the protocol.

**Expected Benefits and / or foreseeable risks to persons**No specific individual results are expected from the study. In the exceptional case where, for a given individual, the study would highlight a health risk, relevant data are communicated to the occupational physician who can communicate the most relevant information to the individual case, in the context of respect for persons and medical confidentiality.

**Risks of the diet.**

There are no adverse effects. The products have been marketed for several years. They were used in a previous study conducted in 2007 and no problems were reported.

**Risks related to metabolic investigations.**Biological samples: The possible inconvenience is related to catheter placement and the possibility of bruising. Good permeability of the catheter is provided by the presence of heparin, it is possible that a very small amount of heparin happens in the body without any risk for clotting.

*Aspiration of abdominal fat*: It is performed under local anesthetic, the potential inconvenience can be a hematoma, of modest size that is resolved in a few days.

*Of DXA:* It is safe and provides radiation in the range of 70-140 kV. (less than a chest X-ray). The test takes about ten minutes.

**Constraints of the test.**

The regulation of clinical trials in humans, has forbidden participation in two contradictory experiments simultaneously. If the subject agrees to participate in this study, they should not participate in another trial with diets or drugs during the same period.

# Practical realization of the study

## Detailed description for the acts realised on the participants:

**Nutritional and inflammatory profiles**

We will evaluate lipid profiles and the glycemic contrôle of subjects before and after each periode. At each time point after overnight fast.at 8h00, blood samples will be taken for measurements plasma glucose, insulin, total cholesterol, LDL- and HDL-cholesterol, triglycerides, leptin and adipnectin.Inflammatory markers: CRPus, and IL6 will be also measured by radio immunologic method or by ELISA) and plasma LPS.

Insulin sensitivity will be estimated by a an oral glucose tolerance test after a charge of 75g of glucose .Blood samples will be taken at 30 min , 60 min et 120 min to measure plasma glucose and insulin..

Body fat and fat-free mass distributions were measured using dual-energy X-ray absorptiometry (Hologic APEX, discovery W. (S/N 84030), version 3.0, Bedford, MA

An sample of subcutaneous abdominal adipose tissue will be taken by aspiration with a fine needle under local anaesthesia (1% xylocaine without isoprenalin).

Two supplementary tubes of blood (7 ml) will be taken to measure other new markers that will be identified by the transcriptomic approch

After 7days of the beginning of the dietary program one tube of blood (1 tube of 10 ml) and an adipose tissue biopsy will be taken to evaluate the early kinetic changes of weight loss and the inflammatory markers in adipose tissue.

**Adipose tissue sampling :**

Subcutaneous abdominal adipose tissue samples will be realised by aspiration with a fine needle (300-500 mg) during the inclusion and at the follow up visits. The aspiration of adipose tissue by a needle is a routine test in the department of Nutrition at the Pitié Salpetrière that is realized by an investigator. A fresh aliquot was collected to measure adipocyte diameter, as described previously (14), and another aliquot was stored overnight at 4°C in 4% paraformaldehyde and embedded in paraffin for immunistochemical detection. A third aliquot will be rapidly put in liquid nitrogen then stored at -80°C till the extraction of ARN.

At the end of the study, all the samples will be conserved for future re-evaluation of eventual gene and protein expressions changes.

**Treatment of biological samples**

The serum samples to be assayed for markers of adiposity and inflammatory factors will be analyzed at our Inserm Unit U872 (Eq 7). The serum bank will be stored by the Inserm Unit U872 (Eq 7). The experiments in adipose tissue will be carried out by the Inserm Laboratory U872 (Eq 7) – Research Center in Human Nutrition of Ile de France (Paris 6) who has the necessary equipment for molecular and cellular biology techniques (whole-genome DNA microarray dedicated to inflammation, and real-time quantitative PCR) in collaboration with the functional genomics Inserm network, who develops microarray-specific analysis methods.

1) **Morphology and cellular population**

Adipocyte diameters will be measured for each subject before and after each period.

2) **Gene expression**

The extraction of total ARNs will be done for the freezed tissues using the adapted kit RNasy Mini Kit (QIAGEN, requis, CA) adapté. Due to the small amount of obtained adipose tissue and the difficuklty of rendement, we will use the methode put and validated by the INSER ([name]), who optimized this method in the European network *MolPage*. On the other hand from total adipose tissue we will identify the candidat genes. Associted to the inflammatory markers, the macrophages (CD 68, CD11b, CD163, mannose receptors, CD40), and the adipokines (leptin, adiponectin), that might be associated to the uinflammatory phenomena.

We will identify also the classes of genetic functions that could be associated to these modifications of the inflammation during body weight loss induced by the hypocaloric diet.

We will study the individual kinetics of gene expression by at day 0, day 7, day 28 and day 42 and after the 6 week stabilization period.

**Urine samples collection:** Samples of urine will be also collected at each time point and conserved at – 20°C.

**Faecal sample collection:** Faecal samples were obtained in the morning at each time point for the determination of metagenomics, metabolomics and metaproteomics. Whole stools were self-collected in sterile boxes and stored at -20°C within 4 h, then sampled as 200-mg aliquots will be moved rapidly to the INRA where it will be stored at -80°C until analysis. Before obtaining the large scale profile of metagenomics, seven groups of the known fecal bacteria will be measured by RT-qPCR. Another global qstudy will be realized by the group of [name] of Genoscope, Evry. We will analyse the reactions between the changes of the intestinal flora, biological changes and the adaptation of the inflammation of adipose tissue by integrating our results to those of the metagebnomic results due to statistic materials and competence concerning the functional genomic (clustering) and multivariant analysis. We have this competence in our unit INSERM U872 by the group of [name].

## Organization and logistics of the tests

The diet will be provided and delivered weekly by the CEPRODI-KOT laboratory.

[name] in the CRNH-Ile de France contacts the subjects the night before the study visit to remind them of the appointment and the requirement of consuming the standard meal well prepared in advance.

Dietary advice will be given at the beginning of each participation period, patients will be contacted in the middle of each participation period and a dietician will be contactable at all times. Data collection will be done at the beginning and end of each participation period using a food diary kept for a week.

Data will be entered by the investigator on a specific report form. The CRA of the study will verify that the information is complete. Data will be collected. Re-entering the data electronically will allow for the correction of any data entry errors.

## Flow-Chart

- Recruitment period: 8 months.

In case of study withdrawal due to recurring medical problems, the withdrawn subject will not be replaced.

- Total study duration: 24 months.
- The total duration of participation for each subject will be 12 consecutive weeks.

# PRODUCT CONSUMPTION

Each subject will consume a home-prescribed diet.

# MEDICAL DEVICES

This is a dietary intervention.

# COLLECTION OF HUMAN BIOLOGICAL SAMPLES

- Sample description (DNA, cell types, tissues, fluids,…) :

Blood, urine and fecal samples, as well as adipose tissue samples will be obtained at the beginning and end of study participation.

- Description of sample acquisition:

Blood samples will be obtained at days 0, 7, 42 and 84 (fasting). The collection tubes will be placed at 4°C upon sample collection, centrifuged at 4°C, aliquoted and stored at –20°C until analyzed.

Tissue sample collection (abdominal subcutaneous adipose tissue) (300-500 mg) will be done by fine needle aspiration after local anesthesia is applied (Xylocaine). The adipose tissue biopsies will be immediately frozed in liquid nitrogen and stored at -80°C until used for total RNA extraction.

The urine and fecal samples will be immediately frozen at -80 °C and later used for metagenomic, metabolomics and metaproteomic analysis as specified in the MICRO-Obes project.

Samples will be discarded (as usual) after analysis is completed.

# STUDY MONITORING

## Definition of serious adverse events

Definition of a serious adverse event (SAE): An adverse event is qualified as serious if it corresponds to any event that causes the following to a person involved in a clinical trial sponsored by Inserm:

- death,
- an immediate threat to life,
- hospitalization or prolongation of hospitalization,
- disability or a (temporary or permanent clinically significant) significant or prolonged disability,
- a birth anomaly or defect.

Finally, every serious adverse event will be considered as such by the investigator. However, given the nature of this study in which the research is carried during usual visits of occupational medicine, a serious adverse event is extremely unlikely.

A hospitalization already planned as part of the care of the individual will not be considered as a SAE and is not within the scope of this protocol. However, every SAE occurring during said hospitalization, according to the definitions given above, does enter the scope of this protocol.

## Procedure to follow in case of a serious adverse event

The investigator shall promptly notify of a SAE on the day he hears of the SAEs occurred in research:

Using the SAE declaration form that shall be sent by fax or email to the study sponsor.

Then the information will be sent in attention to: [name], Laboratoire CEPRODI-KOT, Mission Recherche Clinique, [name].

The investigator will also provide any information necessary for the medical assessment of the observation to the sponsor (account of additional tests, pathology, radiology).

The sponsor ask the investigator for additional information.

All documents submitted by the investigator should be de-identified.

The SAE happening after the study should be reported to the sponsor and followed until they are resolved.

The sponsor should report all suspected serious adverse events to the involved CPP and the Direction Générale de la Santé (DGS) without delay and at the latest 7 days after the first day of knowledge of a life-threatening SAE or a SAE leading to death, and within 15 day for other SAE. Any initial statement will be supplemented by a follow-up statement detailing additional relevant information about the SAE in a new period of 8 days after the timing mentioned above.

The sponsor shall send the CPP and DGS an annual safety report taking into account all the safety information available.

The sponsor shall keep detailed records of all adverse events that are reported by the investigators.

In case of occurrence of a new research-related incident that is likely to threat the safety of people involved, the sponsor and the investigator will take appropriate urgent safety measures.

The sponsor shall inform without delay the DGS and CPP of the new incident and, where appropriate, of the measures taken.

## Monitoring of patients in case of occurrence of a serious adverse event

The monitoring of patients that have had a serious adverse event will be provided by the study phycisian.

## New incidents

In case of the occurrence of a new incident related to the research and likely to pose a threat to the safety of the persons involved, the sponsor and investigator shall take appropriate urgent safety measures.

The sponsor shall promptly inform the DGS and CPP of the new incidents and, where appropriate, of the measures taken.

## Independent Monitoring Committee

Research is being conducted during the usual occupational medicine visits, and so there is no need for independent oversight.

# DATA COLLEction and processing

12.1 **Data collection:**

Data in the form of questionnaires will be collected in a report form by the investigators involved in the study. Patient biological sample data will be transcribed using the same system.

**12.2 Data storage prior to electronic data entry:**

The data are stored in locked cabinets on site.

**12.3 Computer data entry:**

Data are digitized as single entries. This will be done under the supervision of [name], scientific officer of the study. Entries are made in an Excel workbook, where each sheet is a different type of parameter. Data will be combined onto a summary sheet and will be exported to the statistical analysis software (SAS). Data safety is ensured by their storage in the 872 Unit server (Team 7), which is secured according to the current rules at Inserm.

**12.4 Description of treatment, verification and validation of the data:**

Computerized data files will be reported to CNIL according to a procedure adapted to this case.

# statistical analysis of the data

**A. Analysis of clinical data and clinical relationships / morphological data and gene expression data.**

Phenotype data will be obtained from the database, anonymously, as usually done. We will analyze the changes in clinical and biological parameters for each individual at baseline and during kinetic monitoring. MANOVA kinetic tests will be used. We will establish correlations between clinical, biological, morphological and gene expression data using logistic regression analysis. In previous years we have acquired the skills to analyze these data (using JMP software, issued by the SAS Institute). For quantitative traits, multivariate analysis will be used (ANOVA, ANCOVA, logistic regression).

1. **Expression studies**

Results from cDNA microarrays will be analyzed by the Inserm Unit U872 (Team 7), where new strategies of oligonucleotide microarray data analysis are being developed. Experimental results will be stored in the SMD database (http://genome-www5.stanford.edu). We will use a certain number of functions developed for R software (steps of filtering, normalization, selection of differentially expressed genes, groups, etc) in order to highlight groups of modified genes. The translation of gene expression data into the corresponding biological mechanisms (commonly called functional analysis or profiling) is considered a major challenge and is an essential step in the elucidation of the biological phenomena underlying the experimental models being studied. Functional annotation will be used to connect sets of genes in the genome with molecular networks that interact within the cell, in order to illustrate the higher order biological information related to metabolic pathways and their regulation. We will search automatic descriptions of enrichment through the databases Gene Ontology (GO) or KEGG (Kyoto Encyclopedia for Genes and Genomes). Our functional analysis will essentially be centered on inflammatory factors and their associated gene networks. Two algorithms, MAGO and FunCluser, have already been designed with this in mind by our team. They automatically link gene transcription microarray data with the genes’ biological roles in order to investigate significant functional changes in the experiment compared to other functions represented on the chip. We will introduce appropriate statistical analysis to take into account multiple testing (False Discovery rate). A computer engineer in the U872 Inserm team will be dedicated to the work of microarray analysis.

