### Number of people to include:

Effective Calculation: 50 subjects are required to show a change in the ratio of microbiota Firmicutes / Bacteroidetes of at least 40% and a standard deviation of 16 by setting the risk to   0.05 and the risk to 0.10 (calculations made after the results of a pilot study with a low calorie diet of 1200 Kcal).

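### MANOVA over visits, together with ending the participation of those who cannot do the study tasks and no attrition allowance, risks a complete-case result selected on adherence

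*Protocol*

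**What the plan says.** Part A of the protocol's section on statistical analysis states the target, "We will analyze the changes in clinical and biological parameters for each individual at baseline and during kinetic monitoring", and then the method, "MANOVA kinetic tests will be used". A later sentence lists ANOVA, ANCOVA and logistic regression for quantitative traits. Part A gives no other method for the visit-to-visit change, and the protocol gives no missing-data rule or analysis population.

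The section on recruitment and exit has two routes out. One is voluntary: "The exit from the study protocol is possible at any time if requested by the participant". The other is imposed: "Participants who cannot perform the tasks related to research will be excluded from the protocol". It does not say whether someone who leaves is measured again.

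On numbers, the sample-size section says "50 subjects are required to show a change in the ratio of microbiota Firmicutes / Bacteroidetes of at least 40" per cent, and the experimental design section selects the same number, 50. The Flow-Chart section says "In case of study withdrawal due to recurring medical problems, the withdrawn subject will not be replaced". The Compensation section pays nothing to a subject who stops before the end.

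**The concern.** A standard repeated-measures MANOVA needs a full set of visit values. If one value is missing, the subject's other values for that outcome leave the test as well.

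The imposed-exit rule adds a second loss, in the conduct of the study. Someone who leaves in week 3 has no Day 42 or Day 84 value, and no later analysis rule can recover it. Following the supplied diet is a large part of what participants are asked to do, so the rule could plausibly reach people who struggle with it. Those people probably lose less weight.

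There is no comparison group, so the within-subject change is the result. Body-weight and fat loss stand first among the main criteria, and the others mostly concern changes during the diet too. An estimate restricted to adherent subjects answers a narrower question than the effect in all who start.

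**Working it through.** **1. The plan's own figure.** Inputs from the section on the number of people to include: change 40, standard deviation 16, alpha 0.05, beta 0.10. Sidedness and the unit of the standard deviation are not stated. I take a two-sided test and read 16 as the standard deviation of the change.

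- Normal formula for a paired change: n = ((1.960 + 1.282) × 16 / 40)² = (3.2415 × 0.4)² = 1.68.
- Exact paired t at a standardized change of 40/16 = 2.5: n = 4 gives 89.9% power, n = 5 gives 98.2%.

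The stated 50 is not reproduced. For 50 to give exactly 90% power (paired t, two-sided), the standardized change would have to be 0.468: a change of about 7.5 with standard deviation 16, or a standard deviation of about 86 with change 40.

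**2. Complete cases.** Assume each visit value is missing independently with probability m. The protocol gives no rate, so m is a range. Complete cases over k visits = 50 × (1 − m)^k. The schedule in the Overview has stool at three visits (Days 0, 42 and 84), so k = 3 for the Firmicutes/Bacteroidetes ratio.

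| m | (1 − m)³ | complete of 50 |
| --- | --- | --- |
| 2% | 0.941 | 47.1 |
| 5% | 0.857 | 42.9 |
| 10% | 0.729 | 36.5 |

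**3. Power, conditional on 50 being right.** At standardized change 0.468 (two-sided paired t), 50 subjects give 90%, 43 give 85% and 36 give 78%. At the protocol's stated ratio of 2.5, five subjects already give 98.2%, so these losses would not matter. Step 3 therefore holds only if 50 is accepted as the requirement.

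**4. Direction and size of a selection effect.** Let a fraction d leave, and let L be the loss that leavers would have shown. Set the completers' mean at 6%, a level the protocol mentions for six weeks (there for poor responders) and used here only as an anchor. Overstatement = 6 − [(1 − d) × 6 + d × L] = d × (6 − L). With d = 20% (assumed):

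| L (%) | overstatement (percentage points) |
| --- | --- |
| 0 | 0.2 × 6 = 1.2 |
| 3 | 0.2 × 3 = 0.6 |
| 6 | 0 |
| 7 | 0.2 × (−1) = −0.2 |

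The estimate is too high if leavers lost less than completers, and too low if they lost more. The protocol gives neither d nor L.

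**The case against.** The strongest reply is that analysis populations and missing-data rules commonly belong in a statistical analysis plan, which may exist. The imposed-exit rule removes people from the protocol, not their collected data from the analysis. It speaks of tasks and does not name diet failure as a ground. ANOVA and ANCOVA are also listed, and a Day 0 to Day 42 comparison needs only two visits. All of this stands. A reader might infer that the plan is certainly completers-only, but the text does not say so.

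Four other strong readings also fail:

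- **That non-performers are not replaced.** The no-replacement rule is tied to recurring medical problems. On replacing people who leave for other reasons, the protocol is silent.
- **That poor biopsy yield removes subjects from everything.** The gene-expression text does begin "Due to the small amount of obtained adipose tissue", but the sentence goes on to a validated method for that situation. A lost tissue value would not delete weight or stool data from an outcome-by-outcome analysis.
- **That power falls to 74%.** This takes 33 complete cases (50 × 0.9⁴ = 32.8) from a four-visit outcome such as adipose tissue and applies them to the stool ratio, which has three visits.
- **That every before/after estimate is biased.** Step 4 shows that the sign can reverse, and nothing in the protocol shows smaller microbiota or inflammatory change in leavers.

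The reply leaves two things untouched. The protocol itself names MANOVA for the kinetics, and its handling of incomplete vectors is a property of that method. The exit rule governs conduct, and a later plan cannot supply measurements that were never taken.

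**Conclusion.** The concern holds as a risk. Followed as written, the named method and the exit rule can produce complete-case estimates selected on adherence, and the enrolment of 50 leaves no margin. Overstated weight loss is the probable direction, on the assumption that leavers lose less. Its size is unknown.

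At three visits, independent missingness of 5% to 10% per visit would leave about 43 to 36 of 50 subjects. The matching fall in power, from 90% to about 85% or 78%, depends on accepting a sample size that its own inputs do not support. The case for change therefore rests mainly on who is represented in the estimate, and less on power.

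**What to change.** 1. **Statistical analysis, part A.** Replace the MANOVA with a linear mixed model for each outcome: visit as a fixed factor, unstructured within-subject covariance, REML, all available data from everyone who starts the diet, and contrasts for Day 0 to 42 and Day 42 to 84.
2. **Recruitment and exit section.** State that participants who stop the diet or cannot complete some tasks are, if they consent, still invited to the V4 and V5 measurements and stay in the analysis.

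Both parts are needed. The mixed model uses incomplete records, but it does not by itself correct drop-out that depends on the unobserved weight loss. Only the later measurements address that.

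The cost is rewording two sections and some extra follow-up effort at visits already scheduled. Retention may be hard, because early stoppers receive no payment and the late visits include a biopsy. The effect estimate may also come out smaller.

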## Category of research :

## Physiopathological study

## Presentation of the experimental design (CF Schéma général : page 2)

A population of 50 obese subjects will be selected after a review of pre inclusion.

After inclusion, subjects follow a low calorie diet of 1200 Kcals for 6 weeks followed by a stabilization phase of 6 weeks. The low calorie diet will be provided and delivered by the laboratory CEPRODI-KOT (attached a list of products offered and a standard menu with products CEPRODI-KOT). Dietary advice will be given at the beginning of each period, patients will be contacted in the middle of each period and a dietician will always contactable by phone or email. The dietician will contact the patient by phone once a week to ensure that there are no difficulties. Data collection will be done at the beginning and end of each period using a food diary kept for one week. The food composition (nutrients) is obtained using a French food composition table.

The stabilization phase of weight will be adjusted depending to the resting energy expenditure (REE) of each patient and will be calculated by the dietician according to the formula of Harris and Benedict :
REE man = 66.473 + (5.003 x height in cm ) + (13.752 x weight in kg) - (6.755 x age)
REE Woman = 655.096 + (1.850 x height in cm ) + (9.563 x weight in kg ) - (4.676 x age)

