# évaluation CRITERIA

**Main criteria:**

• Quantification of body weight loss and the loss of total body fat
• Variation in the microbiota Firmicutes / Bacteroidetes
• Quantification of the reduction of systemic inflammation (CRP -us , IL6 , TNF , serum amyloid )
• Analysis of profiles of gene function ( gene regulatory networks analyzed by microarray ) interacting with inflammatory functions in the kinetics of weight loss
• Quantification of macrophage infiltration by gene and protein markers (CD11b CD68, and pro markers (CD40) or anti- inflammatory (CD163, mannose receptor)): in the subcutaneous adipose tissue before and after weight loss and linking with the reduction of systemic inflammation (CRP -us, IL6, TNF, serum amyloid).
• Analysis of interactions between the changes of the intestinal flora, biological variations and adaptations (including inflammatory) adipose tissue.

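### Section 13.A names logistic regression for associations between continuous measures, but the protocol defines no binary outcome

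*Protocol*

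**What the plan says.** Section 13.A gives three statements of method for the clinical, biological, morphological and expression data:

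- for changes over time: "MANOVA kinetic tests will be used";
- for associations: "We will establish correlations between clinical, biological, morphological and gene expression data using logistic regression analysis";
- for continuous measures in general: "For quantitative traits, multivariate analysis will be used (ANOVA, ANCOVA, logistic regression" closes the list.

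Section 5 sets the questions that these methods must answer. One main criterion asks for macrophage markers in adipose tissue to be related to the fall in systemic inflammation. The only secondary endpoint relates changes in the tissue and systemic inflammatory profile to clinical and biological changes, including insulin sensitivity. A further main criterion concerns the flora: "Analysis of interactions between the changes of the intestinal flora, biological variations and adaptations (including inflammatory) adipose tissue". For that one, the paragraph on faecal sample collection in section 7 relies on "statistic materials and competence concerning the functional genomic (clustering) and multivariant analysis".

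The design is a single group: "A population of 50 obese subjects will be selected after a review of pre inclusion".

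**The concern.** Logistic regression in its ordinary form estimates how the odds of a category depend on predictors. It does not estimate a correlation between two continuous quantities, and it cannot take a continuous outcome until someone has cut it into classes. The protocol speaks throughout of amounts. Systemic inflammation, for example, is to be assessed as "Quantification of the reduction of systemic inflammation", with no threshold attached.

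Two things are at stake. An analyst who follows the sentence literally has to invent a cut-off, possibly after seeing the data. A cut at the median also discards information that a sample of 50 can ill afford to lose. This is not detail left for a statistical analysis plan. The protocol does name a method, twice, and it is the wrong kind for the data it is named for.

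**Working it through.** **Step 1. Is there a binary outcome anywhere?** The measures are body weight, total fat, CRP, IL6, TNF and serum amyloid (section 5); plasma lipids, glucose, insulin and insulin sensitivity (section 3); adipocyte diameter and expression levels (section 7). All are quantitative. The nearest thing to a category is in section 4, in the mention of poor responders in a European project and of 11 of 15 subjects who kept their weight in an earlier study. Both describe past work and set no rule for this trial.

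**Step 2. Which questions does the sentence reach?** Its list covers clinical, biological, morphological and gene expression data. That matches the tissue-to-systemic inflammation criterion and the secondary endpoint. It does not name microbiota data.

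**Step 3. The plan's own figure.** The protocol states no power for any association. Its only calculation concerns something else: "50 subjects are required to show a change in the ratio of microbiota Firmicutes / Bacteroidetes of at least 40" per cent, with a standard deviation of 16, alpha 0.05 and beta 0.10. Reading 16 as percentage points, a two-sided paired formula gives ((1.960 + 1.282) × 16 / 40)² = 1.7, so 50 is not reproduced. That is a separate matter. Here 50 is simply taken as the number available.

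**Step 4. Cost of a median split, if one were made.** Inputs are n = 50 (section 4, assuming no withdrawals), two-sided alpha 0.05, bivariate normal data, and assumed values of r, since the protocol gives none.

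- Power with both variables continuous: Φ(atanh(r) × √(n − 3) − 1.960).
- Splitting one normal variable at its median multiplies r by √(2/π) = 0.798. Only the outcome needs to be split for logistic regression.

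Example at r = 0.40. Continuous: atanh(0.40) = 0.424; 0.424 × √47 = 2.904; Φ(0.944) = 83%. Split: r becomes 0.319; atanh = 0.331; × √47 = 2.267; Φ(0.307) = 62%.

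The formula was checked with 4,000 simulated data sets per value of r, comparing the Pearson test with the likelihood-ratio test of a logistic model that has a median-split outcome and a continuous predictor.

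| Assumed r | Continuous, formula | Continuous, simulation | r after split | Split, formula | Split, simulation |
|---|---|---|---|---|---|
| 0.30 | 56.4% | 57.3% | 0.239 | 38.7% | 41.0% |
| 0.40 | 82.8% | 84.1% | 0.319 | 62.1% | 66.8% |
| 0.44 | 90.0% | 90.6% | 0.351 | 71.1% | 74.4% |
| 0.50 | 96.5% | 96.8% | 0.399 | 82.5% | 84.9% |

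A separate simulation with 3,000 runs gave 57% against 41% at r = 0.30 and 84% against 65% at r = 0.40. With r = 0 the simulated rejection rates were 5.6% (Pearson) and 6.0% (logistic), so the comparison does not disadvantage the logistic test.

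**Step 5. In terms of sample size.** r = 0.44 is the correlation that 50 subjects detect with 90% power when both variables stay continuous. After a split, n = ((1.960 + 1.282) / atanh(0.351))² + 3 = 81 would be needed.

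**The case against.** The best defence is that the plan does not depend on this sentence. Section 13.A also names MANOVA for changes over time, and ANOVA and ANCOVA for quantitative traits. ANCOVA is a linear model for a continuous outcome and accepts continuous covariates. Nowhere is a median split or cut-off mentioned, so the power loss belongs to a step that the protocol does not plan. A cumulative-logit model could even be fitted to ordered values without a split, although the protocol does not say that this is meant.

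Most of this stands. It removes any claim that the analyses are impossible, and it makes the figures above conditional. It does not remove the mismatch. The sentence on associations names logistic regression and nothing else, and the later list includes it for quantitative traits without restricting it to a binary outcome.

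A reader might go further and infer that the link between flora and inflammation can be studied only by dichotomising. The documents do not support that. The sentence in section 13.A does not cover microbiota data, and section 7 gives that link to clustering and multivariate analysis. What remains is a lack of fit between the two places: section 7 does not say which multivariate methods it means, and the only list of such methods, in section 13.A, again contains logistic regression.

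**Conclusion.** The point holds as a wrongly named method, of moderate severity. Section 13.A assigns logistic regression to associations between continuous measures, and the protocol defines no outcome to which it could apply. This touches one main criterion and the only secondary endpoint.

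The size is conditional. If an outcome were split at the median, power with 50 subjects would drop by roughly 12 to 21 percentage points for true correlations between 0.3 and 0.5. This rests on assumed correlations, normal data, a two-sided 5% test, a single split and no withdrawals.

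A reader might also infer that the associations will mislead because they are not adjusted for shared weight loss. The documents do not support that as a defect. The choice of covariates is commonly left to the statistical analysis plan, ANCOVA would allow such adjustment, and weight change may lie on the pathway that the trial sets out to describe.

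**What to change.** Amend section 13.A in three respects:

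1. For associations between continuous measures, name Pearson or Spearman correlation, or linear regression (mixed models where repeated visits are used), with skewed markers such as CRP and IL6 on the log scale.
2. Take logistic regression out of the list for quantitative traits. Keep it only for an outcome defined in advance as binary, with its cut-off stated.
3. State which multivariate methods section 7 means for the link between flora and inflammation, so that sections 7 and 13.A agree.

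The cost is a few sentences. No data, visits or subjects are added, and nothing of value is lost, since logistic regression stays available for a genuine binary outcome.
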